### Statistical considerations

#### Sample size

We will recruit 60 infants (30 in each arm), which is a feasible number given that the NICU at PCH currently admits approximately 120 infants per year who would meet the eligibility criteria. Assuming the covariate-adjusted within-group standard deviation of F_2_-isoprostane levels in term/late pre-term infants is approximately 25 pg/mL [87], we would therefore have 80% power to detect a difference in early versus late PN levels of 16.2 pg/mL and 90% power to detect a difference of 19.1 pg/mL (α = 0.05). Levels of F_2_-isoprostane at birth have spanned a range of approximately 40 pg/mL across 35-40 weeks gestation [87] indicating the minimal detectable difference is clinically relevant. This study will also have adequate power to detect an increase of approximately 20% in mean phenylalanine levels in infants receiving early PN, noting that mean Day 3 levels in extremely low birth weight infants receiving aggressive nutritional therapy were at least 25% higher than that in infants receiving the standard in the study by Blanco et al. [40]. In the majority of study infants, we will collect blood through existing arterial or central venous lines. In a small number of infants (*n* = 5 to10) in whom such access is not available, we will perform venepuncture to collect the blood samples. To account for the possibility that venepuncture may be unsuccessful, we will recruit an additional three infants.

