### Assignment of interventions

#### Random sequence generation

Group assignment will be allocated by the Clinical Trial Pharmacist at PCH using a computer-generated randomisation sequence in a 1:1 ratio in block sizes of 2 and 4 and stratified according to the primary diagnostic category (medical or surgical) to minimise selection bias.

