Summary statistics for main outcome measures will include 95% confidence intervals, and for all endpoints, differences between PN groups will be considered statistically significant whenever the *p*-value is lower than 0.05 without correction for multiple testing.

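### The stated F2-isoprostane detectable differences (16.2 and 19.1 pg/mL) reproduce only for a one-sided 5% test, whereas the analysis rules read as two-sided, giving about 69% and 83% power instead of 80% and 90%

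*Protocol article*

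**What the plan says.** All the inputs are in the Sample size section of the protocol article:

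- Size and allocation: "We will recruit 60 infants (30 in each arm"), with the Random sequence generation section confirming a "computer-generated randomisation sequence in a 1:1 ratio in block sizes of 2 and 4".
- Variability: the "covariate-adjusted within-group standard deviation of F_2_-isoprostane levels in term/late pre-term infants is approximately 25 pg/mL".
- Claimed power: "80% power to detect a difference in early versus late PN levels of 16.2 pg/mL and 90% power to detect a difference of 19.1". The alpha attached to both figures is 0.05. Sidedness is not given.
- Three further infants are to be recruited in case venepuncture fails.

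The Statistical analyses section plans an ANCOVA of group differences at Days 4 and 8. Its closing paragraph sets one rule for every endpoint: a group difference is significant when p is below 0.05, with no multiplicity correction. The same paragraph says "Summary statistics for main outcome measures will include 95% confidence intervals". The Aim and hypothesis section expects lower levels with late PN, and sets the trial's aim as evaluating both benefits and risks. Neither a one-sided nor a two-sided test is named anywhere.

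**The concern.** A power statement is meaningful only for the test that will be run. The article prints an alpha and a pair of detectable differences in one place, and a significance rule and interval level in another. If the first pair belongs to a one-sided 5% test and the second to a two-sided 5% test, the stated power is too high for the planned analysis.

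This is the only quantified power statement in the article. At a true difference of 16.2 pg/mL, a reader of a null result would think there had been a 20% chance of missing it, when the chance is about 31%. The article also uses the minimal detectable difference to argue clinical relevance, so the size of that difference should be right.

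**Working it through.** **Inputs** (all from the Sample size section): n = 30 per arm, SD = 25 pg/mL (already covariate-adjusted), alpha = 0.05.

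**Formulas.** The standard error of the difference is SE = SD × √(1/n + 1/n) = 25 × √(2/30) = 6.455 pg/mL. Power is the probability that a noncentral t variable with df = 30 + 30 − 2 = 58 and noncentrality Δ/SE exceeds the critical value. In the two-sided case the opposite tail is negligible. The critical value is 1.672 for a one-sided 5% test and 2.002 for a two-sided 5% test.

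Noncentrality at the stated differences: 16.2/6.455 = 2.510 and 19.1/6.455 = 2.959.

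**Step 1: reproduce the stated figures.** With the one-sided critical value, power is 79.8% at 16.2 and 90.0% at 19.1. Solving for the difference gives 16.24 pg/mL (80%) and 19.11 pg/mL (90%). Both stated figures are recovered to the decimal given.

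**Step 2: apply the two-sided test.**

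| Quantity | Stated | One-sided 5% | Two-sided 5% |
|---|---|---|---|
| Power at 16.2 pg/mL | 80% | 79.8% | 69.4% |
| Power at 19.1 pg/mL | 90% | 90.0% | 82.9% |
| Difference at 80% power | 16.2 | 16.24 | 18.39 |
| Difference at 90% power | 19.1 | 19.11 | 21.28 |

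The shortfall is about 11 points at 16.2 and 7 points at 19.1. The detectable differences grow by 18.39/16.24 = 1.13 and 21.28/19.11 = 1.11, that is, by 13% and 11%.

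**Step 3: see whether another reading rescues the figures under a two-sided test.**

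- Normal approximation in place of t: power 70.9% and 84.1%; detectable differences 18.1 and 20.9 pg/mL.
- Five degrees of freedom spent on ANCOVA covariates (df = 53): 69.3% and 82.8%.
- All 63 infants evaluable (31 + 32): 71.6% and 84.7%.
- A smaller SD: it would have to be about 22.0 pg/mL (for 16.2 at 80%) or 22.4 pg/mL (for 19.1 at 90%), not about 25.
- A further gain from ANCOVA: not available, because the SD of 25 is already described as covariate-adjusted.

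None of these restores 80% and 90%. For scale only, keeping 16.2 at 80% or 19.1 at 90% under a two-sided t test would take 39 or 37 evaluable infants per arm.

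**The case against.** The strongest reply is that the two-sided reading is an inference. The article gives only an alpha and a p-value threshold. Its hypothesis is directional (lower levels with late PN), and the phenylalanine sentence is also framed as an increase under early PN. A 95% interval is sometimes reported beside a one-sided test, the aim of weighing benefits and risks describes the whole trial and not this one comparison, and a full protocol or analysis plan that is not shown may settle the matter. It is true that sidedness is unstated, so the point has to be put conditionally. But a directional hypothesis does not declare a one-sided test. An undeclared test of differences at p below 0.05 with 95% intervals is two-sided by convention, and a one-sided 5% test would pair with a 90% interval or a one-sided 95% bound. The figures and the significance rule, as printed, do not fit together.

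The second reply concerns weight. The article fixes 60 first as a feasible number and then derives what it can detect. The corrected differences still fall well inside the roughly 40 pg/mL gestational-age range used to argue relevance: 18.4/40 = 46% and 21.3/40 = 53%, against 16.2/40 = 41% and 19.1/40 = 48% as stated. A null result will be read mainly from its confidence interval. All of this stands, and it limits the point to a correction of wording.

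A reader might go on to infer that the phenylalanine claim, "This study will also have adequate power to detect an increase of approximately 20% in mean phenylalanine levels", is wrong too. The article does not support that. It states no power figure to contradict, and the log-scale SD behind the claim is detail that a condensed article may leave to the full protocol.

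**Conclusion.** The point holds in conditional form. The stated F2-isoprostane figures are those of a one-sided 5% t test. Under the two-sided 5% test that the analysis rules imply, power is about 69% at 16.2 pg/mL and 83% at 19.1 pg/mL, and the differences detectable with 80% and 90% power are 18.4 and 21.3 pg/mL. This rests on the article's own inputs (30 evaluable infants per arm, SD 25 pg/mL) and on reading p below 0.05 for group differences with 95% intervals as two-sided. If a one-sided test was intended, the power figures are right, and the defect moves to the undeclared sidedness and the mismatched interval.

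Two stronger readings might be inferred and are not supported. One is that the plan expressly specifies a two-sided test; it does not. The other is that the trial is too small and must be enlarged; the number was set on feasibility, and the correction only changes what that number can detect. This is a should-fix reporting correction.

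**What to change.** State the sidedness in the Sample size section and make the figures match. For a two-sided test, say that with 30 infants per arm, SD 25 pg/mL and two-sided alpha 0.05 there is 80% power for a difference of 18.4 pg/mL and 90% power for 21.3 pg/mL. Alternatively, keep 16.2 and 19.1 pg/mL and give the power as about 69% and 83%. Add the word two-sided to the significance rule in the Statistical analyses section.

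If a one-sided test was meant, declare and justify it before the data are analysed, limit the one-sided rule to the endpoints concerned, and report matching intervals (90% intervals or one-sided 95% bounds).

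The cost is a few words and slightly less favourable figures. No extra infants are needed, and the ANCOVA stays as planned. Under the two-sided option the intervals stay as planned too. The Trial status section reports 54 infants recruited by November 2021, so the useful moment for the correction is before the results are interpreted.

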#### Statistical analyses

Baseline characteristics of study participants will be reported as counts (percentages) for categorical outcomes, and mean (standard deviation) for normally distributed continuous outcomes or median (interquartile range) for skewed continuous outcomes.

The primary ANCOVA analyses will assess differences between the two PN groups in F_2_-isoprostane and log-transformed phenylalanine levels at Days 4 and 8. The analysis will be based on the principle of intention to treat, with the last blood plasma values carried forward for infants discharged prior to the day 8 blood collection. Covariate adjustment will be made for baseline F_2_-isoprostanes/phenylalanine, sex, gestational age, medical/surgical group, and severity of illness scores (Score for Neonatal Acute Physiology with Perinatal Extension-II (SNAPPE-II) [88].

Linear regression will be used for the analysis of the secondary efficacy outcomes (amino acid and fatty acid profiles) and growth outcomes. Trajectories of F_2_-isoprostanes, plasma amino acids and fatty acids will be examined within a mixed-effects regression framework to account for the multiple measures per infant.

Time to full EN, morbidity and respiratory outcomes (duration of hospital/NICU stay, respiratory support/mechanical ventilation) will be analysed as time-to-event data using Cox regression, with data censored at 90 days for non-survivors and survivors not reaching the endpoint within that time. Other clinical outcomes will be reported descriptively.

Appropriate regression analyses will also explore the association of the biochemical markers (F_2_-isoprostane, plasma amino acids and plasma /RBC fatty acids) with the main clinical outcomes.

Regression analyses will assess PN group differences in an unadjusted manner, as well as (jointly) controlled for risk factors including sex, gestational age, medical/surgical group, birth weight z scores and severity of illness scores (SNAPPE-II) [88]. We will investigate independent effects of 1) Medical and surgical groups; 2) Term (≥ 37 weeks’ PMA) and late preterm groups (34 to 36 6/7 weeks’ PMA). Covariate data that can be reasonably judged to be missing at random will be inferred using an appropriate method of multiple imputations.

Summary statistics for main outcome measures will include 95% confidence intervals, and for all endpoints, differences between PN groups will be considered statistically significant whenever the *p*-value is lower than 0.05 without correction for multiple testing.

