## Background

Term and late preterm infants (≥34 weeks of gestation) may suffer from conditions that predispose them to critical illness needing admission to Neonatal Intensive Care Units (NICU). These include persistent pulmonary hypertension of the newborn (PPHN) [1], meconium aspiration syndrome [2], hypoxic-ischaemic encephalopathy (HIE) [3], sepsis [4], critical congenital heart disease [5], congenital diaphragmatic hernia [6], and other major surgical conditions [7].

During periods of acute illness, the provision of enteral nutrition (EN) may be unachievable, which necessitates the use of parenteral nutrition (PN). PN involves the administration of glucose, amino acids, lipids and various micronutrients and is usually indicated in infants in whom EN is contraindicated or delivers insufficient protein and energy requirements [8].

Despite the wide use of PN in NICU, there is limited evidence regarding the optimal time to commence PN in term and late preterm infants [9, 10]. Evidence regarding early versus late PN in term and late preterm infants is limited to the subgroup analysis of 209 term infants [11] from the PEPaNIC trial, a multi-centre RCT of critically ill children (*N* = 1440; birth to 17 years) [12]. In that study, the early PN group received PN within 24 h of admission and late PN group, after 7 days. They reported that, late PN was associated with earlier discharge from the ICU but increased the risk of hypoglycaemia in neonates [11]. Due to the various study limitations and concerns about hypoglycaemia, experts do not recommend withholding PN for 7 days as standard practice [10, 13]. Furthermore, our Cochrane review, which only identified data from the PEPaNIC trial, also concluded that the quality of the evidence was low, highlighting the need for further RCTs [9].

A recent retrospective cohort study found that preterm infants (born between 30^+ 0^ and 32^+ 6^ weeks’ gestation) who were commenced PN within the first 7 days of life had a higher rate of survival but higher rates of necrotising enterocolitis, bronchopulmonary dysplasia, late-onset sepsis and the need for surgical procedures [14].

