## Methods/design

### Aim and hypothesis

Our current RCT aims to evaluate the benefits and risks of early versus late PN in term and late preterm infants. We hypothesise that late commencement of PN will achieve lower (and more physiological) levels of plasma phenylalanine and plasma F_2_-isoprostanes on Day 4 and Day 8 compared to early commencement of PN in term and late preterm infants.

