#### Early PN (standard care or control group)

Infants randomised to ‘Early PN’ will be commenced PN on Day 1 or Day 2 of admission to the NICU.

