#### Late PN (intervention group)

Infants randomised to ‘Late PN’ will commence PN only after the completion of Day 5 of NICU admission. If an infant randomised to ‘late PN’ does not require PN after Day 5, the infant will still be included as being in the ‘Late PN’ group and analysed as such.

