### Study outcomes

#### Primary endpoints

The two primary endpoints of this RCT are levels of (a) plasma phenylalanine (μmol/L) and (b) plasma F_2_-isoprostane (pg/mL) on Day 4 and Day 8 of admission.

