### Data collection following recruitment

#### Blood sample collections, processing and storage

The whole blood volume of 1.4 mL will be drawn from the study infants via IV access placed for clinical purpose or by venepuncture in accordance with the CAHS Neonatology Guideline (Blood sampling: venepuncture, peripheral arterial, UAC, UVC and CVC).

After a blood sample is drawn by nursing or medical staff in NICU, the sample will be transferred on ice at 4 °C for centrifugation at 4 °C within 2 h of collection. Plasma will be extracted and transferred to small cryovials (0.2 mL for amino acid analysis, 0.25 mL for F2-isoprostanes, 0.05 mL for fatty acids). Any remaining plasma will be stored in a 4th cryovial. Following extraction of plasma from the whole blood sample, the remaining RBC cell sample will be stored in a 5th cryovial for RBC fatty acids. The samples will be stored at − 80 °C. Subsequently, the processed plasma and RBC samples will be transported to external laboratories for analyses on dry ice in an esky. We will use World Courier or Lab Taxi for deliveries to external laboratories. Each sample stored will be clearly labelled with a unique identifiable code, sample day and volume. If an infant is discharged from NICU prior to Day 8, we plan to collect the third sample on the day of discharge.

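### Carrying earlier values forward as Day 8 values in the primary analysis can bias the Day 8 contrast, and the plan does not say which sample is carried

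*Protocol article*

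**What the plan says.** All references are to the protocol article.

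- **Primary endpoints** names plasma phenylalanine and "plasma F_2_-isoprostane (pg/mL) on Day 4 and Day 8 of admission". Day 8 is therefore a primary time point.
- **Aim and hypothesis** gives the expected direction: "late commencement of PN will achieve lower (and more physiological) levels of plasma phenylalanine and plasma F_2_-isoprostanes on Day 4 and Day 8".
- **Statistical analyses** specifies ANCOVA at Days 4 and 8 by intention to treat, "with the last blood plasma values carried forward for infants discharged prior to the day 8 blood collection". Multiple imputation is mentioned for covariates only. The next paragraph says that trajectories of F2-isoprostanes, amino acids and fatty acids "will be examined within a mixed-effects regression framework to account for the multiple measures per infant".
- **Blood sample collections, processing and storage** adds: "If an infant is discharged from NICU prior to Day 8, we plan to collect the third sample on the day of discharge".
- **Early PN**: "Infants randomised to ‘Early PN’ will be commenced PN on Day 1 or Day 2 of admission to the NICU". **Late PN**: these infants "will commence PN only after the completion of Day 5 of NICU admission".

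**The concern.** Carrying a value forward assumes that nothing relevant changes between the sample and Day 8. Here the design changes exposure inside that window: a late-arm sample from Day 4 or 5 precedes PN by protocol, while a Day 8 sample may follow two or more days of it. If Day 4 values are carried, the Day 8 contrast becomes partly a repeat of the Day 4 contrast.

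Early discharge is also a post-randomisation event. It reflects recovery and may differ by arm: the Background reports, from a neonatal subgroup of another trial, that "late PN was associated with earlier discharge from the ICU but increased the risk of hypoglycaemia in neonates". The shares imputed may then be unequal.

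Finally, an imputed value enters the ANCOVA as if it had been measured on Day 8, which overstates the Day 8 information. The same section uses multiple imputation for covariates and mixed models for trajectories, so the weakest missing-data method is the one applied to the primary outcome. At stake are the estimate and the error rate of one of the two primary time points.

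**Working it through.** **1. The plan's own figure.** With 30 per arm and SD 25 pg/mL (Sample size), SE = 25 × √(2/30) = 6.455 pg/mL. The stated detectable differences of 16.2 and 19.1 pg/mL are reproduced with a one-sided α of 0.05 (noncentral t, 58 df: 16.24 and 19.11). A two-sided test gives 18.4 and 21.3. That is a separate matter; 16.2 is used below only as a convenient scale for a Day 4 gap.

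**2. Bias formula.** Let pE and pL be the shares imputed in the early and late arms, E_c and L_c the mean carried values, and E8 and L8 the true Day 8 means in the same infants. For the difference early minus late:

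bias = pE × (E_c − E8) − pL × (L_c − L8).

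With an equal share f in both arms this reduces to f × (D_c − D8), where D_c is the difference in carried values and D8 the true Day 8 difference. A positive bias favours the hypothesis.

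**3. Inputs not in the article.** It gives neither the share discharged before Day 8 nor the course of either biomarker. Everything below is assumed: Day 4 gap 16.2, D8 = 0, SE 6.455, two-sided test at 0.05, and the same biomarker course in infants who leave and infants who stay.

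**4. Results, equal shares.** For Day 6 and Day 7 the gap is assumed to close linearly, from 16.2 on Day 4 to 0 on Day 8, so D_c = 8.1 and 4.05.

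| Share imputed | Day 4 value carried | Day 6 value carried | Day 7 value carried |
|---|---|---|---|
| 10% | +1.6; 5.7% | +0.8; 5.2% | +0.4; 5.0% |
| 20% | +3.2; 7.8% | +1.6; 5.7% | +0.8; 5.2% |
| 30% | +4.9; 11.5% | +2.4; 6.6% | +1.2; 5.4% |

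Each cell shows bias in pg/mL, then the type I error (noncentral t). The normal approximation gives 11.7% instead of 11.5% in the worst cell.

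**5. A smaller Day 8 effect instead of none.** With D8 = 8.1 and Day 4 values carried, the bias is f × (16.2 − 8.1): +0.8 at 10% and +2.4 at 30%.

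**6. Sign check.** Suppose levels fall by 10 pg/mL from Day 4 to Day 8 in both arms, with 15% imputed in the early arm and 30% in the late arm. Then bias = 0.15 × 10 − 0.30 × 10 = −1.5 pg/mL, against the hypothesis. The direction depends on the biomarker course and on the shares.

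**7. What is not quantified.** These error rates use the full SE, so they show only the effect of bias; the loss from treating imputed values as observed is not included. Phenylalanine, analysed on the log scale, has no stated SD from which to compute.

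**The case against.** A reader might infer that carry-forward freezes early-arm values on PN and late-arm values before PN, and so must favour late PN. The documents do not support that, for four reasons.

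- The planned discharge-day sample means that the carried value is often later than Day 4, and the table shows how quickly the effect then shrinks.
- Under the EN section, PN stops once enteral intake reaches 80–100% of target or when clinically appropriate. An early-arm infant well enough to leave may already be off PN.
- The Late PN section keeps infants who never need PN in their arm. For them an off-PN value may be the true Day 8 state.
- Eligibility selects infants expected not to tolerate feeds for at least 3 to 5 days, so few may leave before Day 8. Nothing in the article supports a share as high as 30%.

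The evidence that discharge depends on arm comes from a subgroup of another trial with a different late-PN definition, and the Background says the quality of that evidence was rated low. It supports a possible imbalance, not a certain one.

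It can also be said that the planned trajectory models provide a cross-check, that the Day 4 contrast is untouched, and that a likelihood-based model has its own weakness: under missing at random it predicts Day 8 for discharged infants from those still in NICU.

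All of this stands as a limit on direction and size. It does not rescue the rule. The discharge sample is only planned, a Day 5, 6 or 7 value is still analysed as Day 8, and the analysis section does not say which sample is carried. That section also says discharged without saying from where, while the sampling section says NICU; the article counts NICU and hospital stay separately.

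**Conclusion.** The point holds in a conditional form. The plan fixes a carry-forward rule for a primary time point across an interval in which the late arm's exposure changes. The rule can bias the Day 8 contrast and gives imputed values the weight of observed ones.

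The bias runs towards the hypothesis when Day 4 values are carried and the true Day 8 difference is smaller than the Day 4 difference. Outside that case its sign is not determined by the documents. In the assumed scenario its size runs from negligible (10% imputed, Day 7 samples) to about +4.9 pg/mL with type I error near 12% (30% imputed, Day 4 values carried every time). The upper end is an illustration, not a forecast, because neither the share nor the biomarker course is given.

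**What to change.** 1. Make a likelihood-based repeated-measures model the primary analysis for both biomarkers (phenylalanine on the log scale), with the covariates already listed, arm-by-time and baseline-by-time terms, and arm contrasts reported at Day 4 and Day 8.
2. Do not relabel an earlier value as Day 8. Enter discharge-day samples at their actual sampling day, with time modelled so that Day 5 to 7 samples fit, for example with a random intercept or a continuous-time covariance. A two-visit unstructured covariance has no place for them.
3. Keep the carried-forward ANCOVA as a sensitivity analysis to the missing-at-random assumption, stating that the discharge-day sample is the one carried.
4. Reconcile the Statistical analyses and blood sampling sections on which discharge (NICU or hospital) triggers the rule and which sample is used.
5. Report by arm the number discharged before Day 8 and the day of the last sample.

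Cost: wording, and a model of a kind that the article already plans. No new data are needed, and since the biostatistician is blinded to allocation the change can be fixed before unblinding. The price is a possibly slightly wider Day 8 interval and reliance on missing at random, which the sensitivity analysis probes but cannot prove.

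### The covariates named for the amino acid, fatty acid and discharge z-score regressions omit the outcome's own baseline, and neither the unadjusted nor the adjusted version is named as the main one

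*Protocol article*

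**What the plan says.** All of the following is in the protocol article.

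- **Primary model** (Statistical analyses): "Covariate adjustment will be made for baseline F_2_-isoprostanes/phenylalanine, sex, gestational age, medical/surgical group, and severity of illness scores". The outcome's own baseline heads the list.
- **Secondary efficacy and growth outcomes** (same section): "Linear regression will be used for the analysis of the secondary efficacy outcomes (amino acid and fatty acid profiles) and growth outcomes".
- **How those regressions are adjusted** (same section): "Regression analyses will assess PN group differences in an unadjusted manner, as well as (jointly) controlled for risk factors including sex, gestational age", followed by "medical/surgical group, birth weight z scores and severity of illness scores (SNAPPE-II". Against the primary list, birth weight z score has been added and the outcome's own baseline is not named.
- **Repeated measures** (same section): "Trajectories of F_2_-isoprostanes, plasma amino acids and fatty acids will be examined within a mixed-effects regression framework". Whether the first sample is among the modelled measures is not stated.
- **Growth endpoints** (Secondary clinical endpoints): weight, length and head circumference, each as a z score at discharge and as a change from baseline.
- **Blood samples** (Blood sample collections, processing and storage): for an infant who leaves the unit before Day 8, "we plan to collect the third sample on the day of discharge". The plasma is divided as "0.2 mL for amino acid analysis, 0.25 mL for F2-isoprostanes, 0.05 mL for fatty acids".
- **Significance rule** (end of the statistical section): every endpoint is judged at p below 0.05, with no multiplicity correction.

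**The concern.** Within one section the plan uses the baseline for the two primary markers and does not name it for the remaining outcomes. Phenylalanine would be analysed with its baseline. The other amino acids, measured by the same assay on the same plasma, would be analysed without theirs as far as the named covariates go. Fatty acids, and length and head circumference z scores at discharge, are in the same position.

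Two things are at stake in a trial of 30 infants per arm. First, precision that is already paid for is not used, and an infant's starting level stays in the group comparison as noise. Second, each endpoint yields an unadjusted and an adjusted result with neither declared the lead. For growth alone this is 3 measures × 2 forms (discharge, change) × 2 versions = 12 results, each held to an uncorrected 0.05. That leaves room to emphasise whichever result is more striking.

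**Working it through.** **1. Are the baselines available?** The Day 8 or discharge sample is the third, so one sample precedes Day 4. The primary ANCOVA needs baseline phenylalanine, which comes from the full amino acid assay, so the other amino acids are measured with it. The plasma split includes a fatty acid aliquot, and the remaining red cells are kept for red cell fatty acids. Growth change is taken from a baseline, so baseline z scores exist for all three measures. The study schedule figure is not reproduced in the text, so the first sample's exact timing cannot be confirmed.

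**2. The plan's own figures.** No precision or power figure is given for amino acids other than phenylalanine, for fatty acids or for growth. The figures in Sample size concern F2-isoprostanes: SD 25 pg/mL (already covariate-adjusted), 30 per arm, α = 0.05, detectable differences 16.2 and 19.1 pg/mL. They reproduce with a one-sided t test (16.24 and 19.11). A two-sided test gives 18.1 and 20.9 by normal approximation. Sidedness is a separate matter and does not enter what follows, which uses two-sided 5%.

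**3. Formulas.** Let ρ be the within-group correlation between baseline and outcome, with equal variances. Relative to an unadjusted final value:
- variance with baseline adjustment (ANCOVA): 1 − ρ²
- variance of a change score: 2(1 − ρ)
- ANCOVA relative to change score: (1 + ρ)/2
- detectable difference at 80% power, unadjusted: √(2/30) × (1.960 + 0.842) = 0.258 × 2.802 = 0.72 SD; with baseline, multiply by √(1 − ρ²)

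**4. Results.** ρ is not in the documents. The values below are assumptions, and any precision gained from the other covariates is ignored.

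| ρ | ANCOVA variance | Change-score variance | SE reduction, ANCOVA vs final value | Detectable difference with baseline (SD) |
|---|---|---|---|---|
| 0.2 | 0.96 | 1.60 | 2.0% | 0.71 |
| 0.3 | 0.91 | 1.40 | 4.6% | 0.69 |
| 0.5 | 0.75 | 1.00 | 13.4% | 0.63 |
| 0.7 | 0.51 | 0.60 | 28.6% | 0.52 |
| 0.8 | 0.36 | 0.40 | 40.0% | 0.43 |

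At ρ = 0.8, ANCOVA against a change score gives (1 + 0.8)/2 = 0.90 in variance, and √0.90 = 0.949, so the SE is only about 5% smaller.

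**5. Chance imbalance.** The baseline difference between arms has SD √(2/30) = 0.26 SD units. An imbalance b shifts a final-value estimate by ρb and a change-score estimate by (ρ − 1)b. For b = 0.26 these are:
- ρ = 0.3: +0.08 and −0.18 SD
- ρ = 0.5: +0.13 and −0.13 SD
- ρ = 0.7: +0.18 and −0.08 SD

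The two growth analyses err in opposite directions. With baseline as a covariate, and the other covariates the same, discharge and change models give the same treatment effect.

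**The case against.** The strongest reply is that this is a condensed article and its covariate list is open: it names risk factors *including* five variables, so a full analysis plan could add the baseline. That is fair as far as it goes. But an open list does not put the baseline into the stated models, and the same section did name it where it was wanted. The point rests on the contrast between two stated lists and on the missing lead model, not on a gap in detail.

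Other parts of the reply stand and limit the point.

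- **A reader might infer that the baseline is unused for all these outcomes.** The text does not support that. Three of the six growth endpoints subtract it. Birth weight z score is at least a near-baseline for weight; the article does not say whether the growth baseline is birth or admission, and infants may be up to 28 days old. The mixed-effects trajectories of amino and fatty acids may include the first sample.
- **A reader might infer that the estimates are biased.** They are not on average: allocation is random, and the confidence intervals reflect the chance variation. The shifts in the working are conditional on a given imbalance, and no plausible effect is stated for any secondary outcome against which to call them large.
- **A reader might infer a gain like doubling the trial.** At ρ = 0.7, 60/0.51 is about 118 infants. At ρ = 0.3, 60/0.91 is about 66. Nothing in the document favours either value. A low correlation is quite possible for amino acids in sick infants whose nutrition differs by arm between the first sample and Day 4.

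Reporting unadjusted beside adjusted results is also conventional, and the adjusted version does contain the stratum. The Discussion says the trial is not powered for the clinical outcomes, which include growth.

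**Conclusion.** The point holds as a free improvement of modest severity. The covariates named for the linear regressions of Day 4 and Day 8 amino acids, fatty acids and discharge z scores omit the outcome's own baseline, although it is collected and the primary ANCOVA uses it. An unadjusted version without the randomisation stratum is also planned, and no version leads.

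The consequence is lost precision and retained chance imbalance. For assumed correlations of 0.3 to 0.7, the SE reduction forgone against an unadjusted final value runs from about 5% to 29%. This assumes equal baseline and outcome variances and takes no account of the other covariates, so the gain over the planned adjusted model could be smaller. For growth the change score already recovers much of the gain when the correlation is high. The primary analyses are not affected.

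**What to change.** In the Statistical analyses section or the SAP, before any comparison by arm:

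1. Add to the adjusted model the baseline value of the same analyte (log scale where skewed) or the same z score, and state whether the growth baseline is birth or admission.
2. Keep the medical/surgical stratum in that model.
3. Name that model as the main analysis of each secondary efficacy and growth endpoint. Unadjusted results and raw changes can be shown as supportive.
4. Say whether the mixed-effects trajectories include the first sample.

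The cost is wording and one degree of freedom per model, with no new data or samples. Trial status shows recruitment still open when the article was written, and the biostatistician is blinded to allocation. If the data have not been unblinded, the change can be made without knowledge of results.
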